## **4.2 Eligibility**

### **Inclusion criteria**

- Histologically documented, untreated prostate adenocarcinoma, (small cell acinar type).
- Patients must have had an extended pattern biopsy (defined as 8+ cores) within 2 years of the screening date. Potential subjects who meet all of the eligibility criteria EXCEPT for the aforementioned extended pattern biopsy within two years of the screening date, may enroll in the study if they have an extended pattern clinical biopsy scheduled within 6 weeks of the Intervention start date. They must also be willing to have an additional 4 biopsy cores taken for research at this appointment, as well as have the other baseline data collected (QOL, FFQ, 3-day food diary, blood and urine specimens, and a H and P) prior to this biopsy. If the extended pattern clinical biopsy does not meet the inclusion criteria, they will be dropped from enrollment. Final eligibility will be determined after a review of the extended pattern clinical and research biopsy cores by the UCSF Department of Pathology. The purpose of this is to avoid an additional biopsy. If a patient has had a biopsy outside of UCSF, a UCSF pathologist must review the biopsy slides [UCSF pathology review of the most current biopsy slides that indicate malignancy].
- Patients must have 3 serum PSA levels done at least 2 weeks apart over the past year prior to randomization.
- Patients must have PSA  $\leq 10.0$ , (PSA  $< 15$  will be allowed for trial eligibility for patients with benign prostatic hyperplasia or prostatitis), Gleason sum  $\leq 6$  with no pattern 4 or 5 histology (if Gleason pattern 4 is seen as a microfocus [ $< 2\text{mm}$  in length])

this will not exclude the patient from trial eligibility), and clinical stage T1 or T2a.

Patients must have no more than 33% of biopsy cores positive (if  $\geq 33\%$  of biopsy cores are positive due to microfoci of adenocarcinoma, this will not exclude the patient from trial eligibility), and no more than 50% of the length of a tumor core involved by carcinoma. These criteria are based on the literature in watchful waiting[59, 60], and are expected to minimize the risk that a patient would develop metastatic disease as a result of participating in the study.

- Life expectancy of greater than 3 months and ECOG performance status  $\leq 2$  are required
- Ability to understand and willingness to sign an informed consent document.

### **Exclusion criteria**

- Any prior or concurrent treatment for prostate cancer, including surgery, radiation, hormonal therapy (Lupron, Casodex, Flutamide, Zoladex, Megace, Nilutamide, DES/estrogen), chemotherapy, PC-SPES, or investigational agents.
- Patients with PSA doubling time < three months are ineligible.
- Use of lycopene, fish oil, or any other preparation intended to supplement levels of omega-3 unsaturated fatty acids within 4 weeks of study entry and during the 3-month intervention period.
- Use of Finasteride, Dutasteride, Saw Palmetto or any other herbal/nutritional preparation indicated to affect hormone levels within 4 weeks of study entry and during the 3-month intervention period.
- Use of NSAIDs, Cox-2 inhibitors, and/or aspirin for more than 7 days over the one month prior to study enrollment and during the 3-month intervention period.
- History of allergic reactions attributed to tomatoes, fish, soybean oil, gelatin capsules, or compounds of similar chemical or biologic composition to lycopene (carotenoids) or fish oil.

- Uncontrolled intercurrent illness including, but not limited to, ongoing or active infection, symptomatic congestive heart failure, unstable angina pectoris, cardiac arrhythmia, or psychiatric illness/social situations that would limit compliance with study requirements.

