### **5.3 Duration of therapy**

Treatment will continue for 90 days, or until follow-up biopsy is scheduled (the maximum duration of treatment will be 104 days). During the planning process for this protocol, we met with prostate cancer advocates and support groups. At these town hall meetings, we learned that more than 50% of men eligible for watchful waiting were already taking a variety of nutrition supplements. The men in these groups expressed willingness to forgo their usual regimen for a period of three months, but they felt that continuing to 6 months or 12 months would deter them from participating in the study. Thus, to aid in rapid accrual, we have selected a three month duration for the intervention. Based on other preliminary studies[41], this 90 day period will be sufficient to observe biological changes in target prostate tissue.

Other pertinent info about administration

None.

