### **8.2 Screening assessments**

#### **Baseline assessment—Clinical**

Before beginning the study a medical history and physical examination, including a digital rectal exam, will be done. On entry into the study, patients will undergo a limited core biopsy by [name] or another urologist from the UCSF Urologic Oncology Department to procure fresh tissue for genomic analysis. Patients who have already donated core biopsies at the time of diagnosis for the Prostate Cancer Tissue Bank will be asked to participate if they meet the inclusion criteria, but will not need to be re-biopsied. Standard clinical history and physical exam, including digital rectal exam, will be performed, and serum will be assayed for PSA, free PSA, testosterone, estrogen, lycopene, omega-3 fatty acid, omega-6 fatty acid, IGFBP-3, and IGF-1. Tissue biopsies for research purposes will also be sent for standard pathologic examination. All patients will fill out a survey instrument characterizing their dietary habits, the Willett SFFQ, a validated food questionnaire as well as a food diary to be completed daily for 3 days prior to the biopsy. All patients will also complete a Health and Prostate Cancer Survey at baseline and at 3 months.

In addition to any prostate biopsy obtained above, serum and urine will be obtained and frozen for future analysis. These samples will be used to investigate the presence of any proteins identified in the gene discovery process. There is currently a CHR protocol in place (99394 CHR#H7720-10671-05) for the collection of cancer specimens for the study of molecular changes.

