bpatients who have donated prostate needle biopsy tissue within 3 months of study entry to the existing Prostate Cancer Tissue Bank will not undergo the initial TRUS biopsy, since their gene expression pattern will have already been comprehensively assessed, and RNA for the primary study aims banked.

cneed for the 12 month TRUS biopsy will be determined by the PSA progression criteria in section 9.4. Some patients, specifically those whose PSA doubling time remains > 12 months at the final study visit will not be asked to undergo the 12 month biopsy.

d three serum PSAs at least 2 weeks apart over the past year to permit calculation of a PSA doubling time [77] must be available. For those patients without serial PSA measurements, randomization will be delayed until collection of the third PSA. Patients with PSA doubling time < 3 months are ineligible to participate.

ePatients will remain on the assigned intervention – placebo, lycopene or fish oil, until the follow-up appointment for transrectal ultrasound and prostate biopsy occurs. Due to scheduling constraints, such as the occurrence of weekends or holidays, it is anticipated that some patients may have to stay on supplement between one to two weeks longer than the literal three month period. Any patient where repeat biopsy cannot be obtained by 14 weeks after beginning intervention will be censored.

fSerum and urine are banked at study entry but not used in the primary data acquisition. These resources are anticipated for possible future confirmatory studies if predictors of progression are identified. Patients will initial their consent for these samples at the end of the informed consent form.

gThe three month research biopsies will be performed at no cost to the participating study subjects.

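### For men whose baseline is banked tissue, the exclusion windows run from study entry and not from the biopsy, so about two months of possible exposure to excluded agents are left uncovered

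*Protocol*

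**What the plan says.** Protocol section 4.2 (Exclusion criteria) sets three windows, none of which mentions the baseline biopsy:

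- Lycopene and omega-3 products: "Use of lycopene, fish oil, or any other preparation intended to supplement levels of omega-3 unsaturated fatty acids within 4 weeks of study entry".
- Hormone-active agents (finasteride, dutasteride and saw palmetto are named): the same 4 weeks before entry, and then throughout the intervention.
- Anti-inflammatory drugs have their own rule, worded as "Use of NSAIDs, Cox-2 inhibitors, and/or aspirin for more than 7 days over the one month prior to study enrollment". This is a limit on use, since up to 7 days are tolerated.

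The default baseline (section 8.2, clinical baseline assessment) is a limited core biopsy on entry. There is one exemption, in footnote b of the study table (section 8.6): "patients who have donated prostate needle biopsy tissue within 3 months of study entry to the existing Prostate Cancer Tissue Bank will not undergo". What these men skip is the baseline TRUS biopsy. The reasons given are that their expression has already been assessed and "RNA for the primary study aims banked". Section 8.2 gives the same exemption for cores donated at diagnosis: such men "will be asked to participate if they meet the inclusion criteria, but will not need to be re-biopsied". No age limit for the tissue is stated there.

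Section 13 defines the primary outcome as at least a two-fold decrease in IGF-1 or COX-2 at three months relative to the man's initial biopsy. The proportions in each supplement arm and placebo are compared by Fisher's exact test.

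**The concern.** For a banked-tissue man, the denominator of the primary endpoint is expression in tissue that may be up to 3 months older than the date from which the windows are counted. The protocol hypothesises that lycopene lowers IGF-1 and fish oil lowers COX-2 (section 2.1). On that hypothesis, a man already taking the matching agent at his banked biopsy starts from a suppressed level and has less room for a two-fold fall. If he is assigned placebo, his change includes the effect of having stopped. Neither is the contrast intended, which is agent-free tissue against tissue after three months of assigned treatment.

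The same gap applies to NSAIDs, Cox-2 inhibitors and aspirin, which the protocol restricts and which bear on the COX-2 pathway. The analysis cannot separate these men later unless their agent use at the biopsy date has been recorded.

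**Working it through.** **1. Dates.** Inputs are the 4-week and one-month windows (section 4.2) and the 3-month limit on banked tissue (footnote b). Take 3 months as 91 days and one month as 30.

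- Lycopene, omega-3 and hormone-active agents: 91 − 28 = 63 days uncovered.
- NSAIDs, Cox-2 inhibitors, aspirin: 91 − 30 = 61 days uncovered.

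Example: a man's tissue is banked 10 weeks before entry while he takes fish oil, and he stops 5 weeks before entry. The omega-3 exclusion looks back only 4 weeks, and 5 > 4, so it does not exclude him. His biopsy meets the 3-month limit. His baseline COX-2 was nevertheless measured on fish oil.

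**2. The plan's own figures.** Inputs from section 13 are 20% v 60%, 29 per arm, a directional test at .025, 81% power, Fisher's exact test and 10% dropout.

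- The normal-approximation sample size with continuity correction is 28 per arm, against 29 stated.
- Accrual: 87 / 0.90 = 96.7, rounded up to 97, as stated.
- Exact power is the sum, over all pairs (x placebo responders, y active responders), of Bin(x; 29, p₀) × Bin(y; 29, p₁), counting pairs where the one-sided Fisher p-value is at most .025. With p₀ = 0.20 and p₁ = 0.60 this gives 83.0%, slightly above the stated 81%.

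**3. Effect of on-agent baselines.** Let f be the share of men in a comparison whose baseline was taken on the relevant agent. The documents do not give f. Assume that affected men on the matching arm respond at the control rate of 20% and that placebo stays at 20%. Then p₁ = 0.60(1 − f) + 0.20f = 0.60 − 0.40f.

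| f | p₁ | Exact power |
|---|---|---|
| 0 | 60.0% | 83.0% |
| 2% | 59.2% | 81.4% |
| 5% | 58.0% | 78.7% |
| 10% | 56.0% | 73.9% |
| 20% | 52.0% | 63.1% |

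**4. Sensitivity to the response assumption.** Suppose affected placebo men respond at 5%, because stopping the agent lets expression rise. Then p₀ = 0.20 − 0.15f, and power is 82.1%, 80.8%, 78.5% and 73.7% for f = 2%, 5%, 10% and 20%. The loss is smaller but in the same direction.

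**5. How large might f be?** An affected man must have a banked baseline, taken more than about 4 weeks before entry. He must have been on the relevant agent then, and have stopped in time to be eligible. Purely as an illustration with assumed shares, 40% banked × 60% older than 4 weeks × 20% on the agent = 4.8%, before counting who stopped in time.

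**The case against.** The strongest reply is that the subgroup may be tiny and the response assumption is harsh. Several conditions must hold together, none of their shares is documented, and step 3 removes the whole supplement effect in every affected man. At f = 2% power is still 81.4%, above the protocol's 81%. This stands, and it limits the size of the point. It does not remove the gap.

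Three stronger readings are tempting, and the documents do not support them.

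- **That the 6-week biopsy route has the same gap.** Section 4.2 admits men if "they have an extended pattern clinical biopsy scheduled within 6 weeks of the Intervention start date". That route is open only to men who already meet every other eligibility criterion, and their food questionnaire, diary and blood are collected before that biopsy. The gap belongs to banked tissue.
- **That most men are affected.** Section 5.3 reports that "more than 50% of men eligible for watchful waiting were already taking a variety of nutrition supplements". This covers any supplement, not lycopene or fish oil in particular. It also describes men already facing the choice of watchful waiting, whereas section 8.2 speaks of cores donated at diagnosis. Supplements begun because of the diagnosis would come after that tissue. The figure gives no value for f.
- **That the trial is biased towards a positive result.** Exposure at the banked biopsy precedes randomisation, so it is balanced across arms in expectation. The type I error is not inflated by it.

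**Conclusion.** The point holds for men whose baseline is banked tissue, and only for them. A site that follows the protocol exactly can enroll a man whose primary-endpoint baseline was taken on an excluded agent, and no record would show it. The uncovered period is about two months under footnote b. Section 8.2 read alone sets no limit.

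The consequence is dilution of the supplement effect and lost power. Under the assumption of step 3, the loss is under 2 points at f = 2%, about 4 at 5%, 9 at 10% and 20 at 20%. It is smaller if placebo men show a withdrawal effect. All of these rest on an assumed f and an assumed complete loss of effect. The timing mismatch itself rests on the text alone. This is an inexpensive improvement worth making; it does not invalidate the design.

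**What to change.** Reconcile section 4.2 (Exclusion criteria), section 8.2 (clinical baseline assessment) and footnote b of the study table, so that the existing exclusion windows also refer to the date of the biopsy used as baseline. The same edit should settle whether the 3-month limit in footnote b governs section 8.2.

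For every man using banked tissue, record use of the listed agents at that biopsy date, including men already enrolled. This is a pre-randomisation fact and can be collected without knowledge of the arm. Report the primary Fisher comparison for all evaluable men and again without on-agent baselines. Because the subset is defined before randomisation, dropping it keeps the comparison fair.

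The cost is one screening question and one sensitivity analysis on slightly fewer men. The 29 per arm and the accrual of 97 are unchanged.

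If the sponsor also withdraws the exemption for tissue taken on an excluded agent, the cost is greater and should be stated. Those men would need the default baseline biopsy or would not enter. Section 10.5 attributes discomfort and a small added risk of bleeding or infection to an extra biopsy, and bills biopsies other than the three-month one to patients or insurers.

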### 4.3 Inclusion of women and minorities

Since women do not get prostate cancer, they are not eligible for this study. Men of all ethnic groups are eligible to participate. The proposed study population, based on accrual to an existing prostate gene expression study is illustrated in the table below.

| Race/Ethnicity                |                               |          |                           |         |       |
|-------------------------------|-------------------------------|----------|---------------------------|---------|-------|
| White, not of Hispanic Origin | Black, not of Hispanic Origin | Hispanic | Asian or Pacific Islander | Unknown | Total |
| 63.4%                         | 14%                           | 4.3%     | 13%                       | 4.3%    | 100%  |

### 4.4 Total number

Assuming independence of genes, 29 patients will be randomized to the lycopene intervention, 29 to the fish oil intervention and 29 to the control arm. This total evaluable sample size of 87 is sufficient to detect 60% of the intervention arm showing two-fold decrease in *IGF-1* and *Cox-2* gene expression compared with 20% of the control group. An additional 10 patients will be entered for a total planned accrual of 97, assuming a 10% dropout rate (final evaluable target number in each arm is 29). (see statistical considerations, below).

### 4.5 Recruitment

Patients are referred to the program in Urologic Oncology at Mt. Zion hospital for clinical management of prostate cancer. All those who meet the inclusion criteria will be invited to participate at the time of the office consultation. The study will be presented to eligible patients by treating physicians, who will obtain consent from those agreeing to participate.

### 4.6 Method of treatment assignment and blinding

Patients will be stratified prior to randomization based upon their dietary intake of tomato and fish. Four strata have been defined (low tomato, low fish; low tomato, high fish; high tomato,

low fish; and high tomato, high fish) using the results from a pilot study of 96 subjects. The cutoff for low vs. high tomato-product intake will be four servings/week; the cutoff for low vs. high fish intake will be two servings per week. Patients will be randomized from within each of the 4 strata to one of the 3 study regimens (placebo, lycopene or omega-3) with equal probability. This will ensure that there is a balance of patients based upon current dietary intake among the 3 arms. Treatment assignment will be balanced after every 9 patients are randomized within each stratum. Because the distribution by strata is unknown the block size is small to avoid an imbalance as the study approaches conclusion. As indicated each intervention arm will be compared with the placebo group so it is important to maintain a balance in baseline diet as to lycopene and omega-3 in each of the 3 study arms.

Data on usual intake in this trial will be assessed at baseline by the same dietary survey used in the pilot study.

In the control arm (arm 1), patients will maintain their usual diet and take placebos representing lycopene and fish oil. In the lycopene arm (arm 2), patients will take 30mg of lycopene and a placebo representing fish oil, in the omega-3 arm (arm 3), they will take 3g of fish oil daily, and a placebo representing lycopene.

## 5 Treatment Plan

### 5.1 Table of drug administration

| Drug                                  | Dosage         | Administration vehicle/volume | Route | Instructions     | Starting Date | Duration |
|---------------------------------------|----------------|-------------------------------|-------|------------------|---------------|----------|
| Lycopene                              | 30mg           | 15mg softgels                 | Oral  | 2 softgels daily | Day 1         | 90 days  |
| Lycopene Placebo                      | N/A            | Placebo softgel               | Oral  | 2 softgels daily | Day 1         | 90 Days  |
| Fish oil
EPA=1098 mg
DHA=549 mg | 3g             | 1000mg softgels               | Oral  | 3 softgels daily | Day 1         | 90 days  |
| Fish Oil Placebo                      | Not applicable | Placebo Softgel               | Oral  | 3 softgels daily | Day 1         | 90 days  |
| Multivitamin                          | Tab            | Capsule                       | Oral  | 1 daily          | Day 1         | 90 days  |

### 5.2 Written description of drug dosing

Patients will take placebo, lycopene or fish oil supplements daily, as oral preparations, on an outpatient basis. The investigational pharmacy at the Cancer Center will maintain an excel

spreadsheet which will record the number and type of placebo, fish oil and lycopene capsules dispensed. In addition, to counter the possibility that different vitamin preparations could affect study results, patients will be asked to cease their usual vitamin intake and use a standard multivitamin (that we will provide). Patients must refrain from taking any other supplements, herbs, or other treatments during the 3-month intervention period.

### **5.3 Duration of therapy**

Treatment will continue for 90 days, or until follow-up biopsy is scheduled (the maximum duration of treatment will be 104 days). During the planning process for this protocol, we met with prostate cancer advocates and support groups. At these town hall meetings, we learned that more than 50% of men eligible for watchful waiting were already taking a variety of nutrition supplements. The men in these groups expressed willingness to forgo their usual regimen for a period of three months, but they felt that continuing to 6 months or 12 months would deter them from participating in the study. Thus, to aid in rapid accrual, we have selected a three month duration for the intervention. Based on other preliminary studies[41], this 90 day period will be sufficient to observe biological changes in target prostate tissue.

Other pertinent info about administration

None.

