### **3. On-study guidelines, study design**

#### **3.1 General study design**

We propose a randomized placebo-controlled trial of lycopene and fish-oil supplementation among men with newly-diagnosed, favorable-risk prostate cancer who opt for watchful waiting as their primary treatment strategy. Our main outcome will be changes in gene expression in prostate tissue biopsies taken before and after the three-month intervention period. Men will provide dietary surveys and records prior to each biopsy (i.e. before and after the three-month intervention). Serum levels of lycopene and omega-3 fatty acid will be measured before and after the intervention to assess compliance and to conduct correlative analyses.

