### **8.3 Assessment during the treatment period**

#### **Follow-up assessment—Clinical**

Standardized Clinical Follow-up Protocol - At the three month follow-up, patients will undergo a standard history and physical exam including digital rectal examination performed by the treating physician. Serum and red blood cells will be drawn for PSA, testosterone, estrogen, lycopene, omega-3 fatty acid, omega-6 fatty acid, IGFBP-3, and IGF-1 levels. Patients will have a second appointment for research purposes only, with a study urologist ([name] or another urologist from the UCSF Urologic Oncology Department) who will obtain four directed prostate core needle samples under ultrasound guidance in order to re-biopsy the areas of tumor and normal prostate identified at the baseline visit to fulfill the study primary outcome measure of detecting gene expression modulation by nutrients. Tissue biopsies for research purposes will also be sent for standard pathologic examination. As obtaining biopsies three months after electing Watchful Waiting is not standard practice, the study will bear costs for the biopsy procedure. In addition to any prostate biopsy obtained above, serum and urine will be obtained and frozen for future analysis. Patients will fill out a second food diary during the second month of treatment intervention and a third food diary prior to their biopsy. These food diaries will be used to collect information about changes in dietary behavior associated with recent diagnosis with prostate cancer, dietary counseling, or participation in this trial. Patients will complete another Health and Prostate Cancer Survey after three months. Patients will also be asked to self-report their compliance with the study treatment, and to return their medicine so that pill counts can be performed. Based on the results of the three-month follow-up visit, serum and pathology tests, the treating physician will assess the patient for disease progression.

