For the secondary specific aims (aims 1.2 through 1.4 defined above), we will consider a microarray dataset with measurements for 30,000 genes. For this exploratory investigation genes will be treated as being independent so as to first identify all possible genes that may indicate an effect due to the nutritional supplement (Aim 1.2) or to other dietary components (each considered as a binomial variable) (Aim 1.3). Fisher's exact test will be used to determine which genes result in differences in proportions with up or down regulated genes between groups. No adjustment for multiple comparisons will be made. Also, after all patients have had the potential to be followed for at least one year, they will be classified as to whether they had experienced disease progression within 1 year from protocol entry. The same exploratory techniques described above first using the baseline gene expression profile will be carried out to identify genes that may be associated with disease progression (Aim 1.4). Even though any nutritional supplement will be stopped at 3 months from the start of protocol therapy and the duration of any effect is unknown, this analysis will be repeated using the 3-month gene expression profile to identify the effects of any gene that might have been modified by protocol treatment. To account for genes with highly variable expression regardless of study arm, genes whose expression levels change two-fold in more than 20% of men on placebo (comparing three-month to baseline) will

be excluded from subsequent consideration. This might exclude possible predictors of outcome, but if there is variability within the placebo group then the results may be biased. This refining process will isolate potential predictors of nutritional change when assessing the primary as well as the secondary outcomes. Standard microarray gene expression software algorithms will facilitate analyses to determine if there are individual genes or clusters of genes associated with either supplement, dietary component or disease progression[62, 63] . Fisher's exact test will be used to determine which genes result in statistically significant differences between the groups.

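### Dosing may run to day 104 and a two-week overrun is expected, but men not biopsied by day 98 are censored; 5.3 and footnote e also end dosing at different events

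*Protocol*

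**What the plan says.** Three places in the protocol set the length of dosing and the timing of the repeat biopsy.

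- **Table 5.1** lists 90 days from day 1 for every supplement and placebo.
- **Section 5.3** qualifies this: "Treatment will continue for 90 days, or until follow-up biopsy is scheduled (the maximum duration of treatment will be 104 days".
- **Section 8.6, study table, footnote e** keeps men on their assigned capsules "until the follow-up appointment for transrectal ultrasound and prostate biopsy occurs". It expects that weekends, holidays and similar constraints will leave some of them on supplement "between one to two weeks longer than the literal three month period". It closes with: "Any patient where repeat biopsy cannot be obtained by 14 weeks after beginning intervention will be censored".

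The repeat biopsy supplies the three-month half of the primary outcome, which is a two-fold fall in *IGF-1* or *COX-2* mRNA from baseline (sections 3.2.1 and 13).

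**The concern.** The treatment maximum and the biopsy cut-off were evidently meant to describe the same window, but they end on different days. Men biopsied in the gap will have followed the treatment rules and provided tissue, yet the footnote removes them from the comparison. I read censoring here as not counting towards the two-fold comparison, because that outcome is binary and needs both biopsies.

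The two places also name different events for the end of dosing. Taken literally, 5.3 lets a man stop once his appointment has been booked, while footnote e has him continue until it happens. Whether the primary-endpoint tissue is taken on supplement should not depend on which page the site staff consult.

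**Working it through.** **Inputs.** Nominal duration 90 days (5.1, 5.3). Treatment maximum 104 days (5.3). Expected overrun one to two weeks past three months, and biopsy cut-off 14 weeks (both footnote e). Two plus three softgels daily (5.1). For scale: 29 evaluable men per arm, 20% against 60%, directional level 0.025, power 81% (section 13).

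**Step 1: reproduce the 104 days.** 90 + 14 = 104. The maximum in 5.3 is the nominal period plus the upper end of footnote e's overrun, so those two statements agree.

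**Step 2: the cut-off in days.** 14 × 7 = 98.

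**Step 3: the gap.** 104 − 98 = 6 days, that is days 99 to 104.

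**Step 4: footnote e against itself.** Counted from day 90, the expected overrun ends between 90 + 7 = 97 and 90 + 14 = 104. Only days 97 and 98 of that range meet the footnote's own cut-off. Counting three calendar months as 89 to 92 days gives 96 to 99 for one week over and 103 to 106 for two weeks over. One week over mostly fits. Two weeks over never does.

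**Step 5: the end of dosing, side by side.** Section 5.3 stops at 90 days or when the biopsy is scheduled. Footnote e stops when the biopsy occurs. Booking comes before the procedure, so these are different days unless scheduled is taken to mean the appointed date.

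**Step 6: scale of the loss, on an assumption.** The protocol does not say how many men would be biopsied on days 99 to 104. Suppose 1 to 3 men per arm were lost in this way beyond the 10% dropout allowance. Exact power is the sum, over all pairs of responder counts, of Bin(x; n, 0.60) × Bin(y; n, 0.20), keeping pairs whose one-sided Fisher p-value is at most 0.025.

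| Men per arm | Exact power |
|---|---|
| 29 | 0.830 (protocol states 81%) |
| 28 | 0.823 |
| 27 | 0.802 |
| 26 | 0.799 |

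Losing three men per arm costs 0.830 − 0.799 = 0.031.

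**Step 7: capsules.** 2 + 3 = 5 softgels a day in every arm. 90 × 5 = 450 and 104 × 5 = 520, a difference of 70.

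**The case against.** The strongest reply is that a ceiling on exposure and a limit on evaluability are different rules and need not share a date. Both can be obeyed: a man biopsied on day 101 was dosed permissibly and is not counted. That is correct, and the analysis does have a stated rule for him. It does not explain why footnote e anticipates a two-week delay as routine and then discards the men to whom it happens.

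It can also be said that scheduled in 5.3 simply means the appointed date, and that footnote e makes the intention to dose until biopsy plain. I accept that as the intention, which is why the remedy is to align the wording.

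A reader might infer more than this, and the document does not support it:

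- **That four different stopping times are stated.** Ninety days and three months are the same nominal period. Table 5.1 gives it, and 5.3 and footnote e extend it.
- **That section 13 sets a conflicting stop.** Its clause that "any nutritional supplement will be stopped at 3 months from the start of protocol therapy and the duration of any effect is unknown" belongs to the discussion of relating three-month expression to progression within one year (Aim 1.4). It is not a dosing instruction, and the uncertainty it mentions concerns the months after dosing ends.
- **That evaluable tissue may be taken up to 98 − 90 = 8 days off supplement.** This requires staff to follow the nominal 90 days and ignore footnote e. If footnote e is followed, the gap is zero.
- **That the exposure blood is mistimed.** Section 8.3 places the assayed blood with the three-month follow-up and says: "Patients will have a second appointment for research purposes only, with a study urologist". No interval is given, the study table puts both in the same column, and they could fall on one day. This is an omission, and the primary Fisher test does not use the serum values.

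**Conclusion.** The inconsistency is real but minor. It consists of a 6-day gap between the treatment maximum and the biopsy cut-off, a footnote whose cut-off excludes most of the delay it expects, and two different events for the end of dosing. It matters because it decides which men count in the primary endpoint.

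The number of men affected cannot be derived from the document, and some or all of them might already fall within the 10% dropout allowance. The power figures in step 6 rest on an assumed loss and show only that even three men per arm would cost about 3 percentage points. Nothing here calls the primary test or the sample size into question.

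**What to change.** 1. In 5.3, replace *is scheduled* with *occurs*, so that dosing runs through the day of biopsy as footnote e intends.
2. In footnote e, change the biopsy cut-off from 14 weeks to 104 days, matching both the treatment maximum and the expected overrun.
3. In table 5.1, mark the 90 days as nominal, and supply capsules for up to 104 days.

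**Cost.** Wording in three places. If only a 90-day supply is now dispensed (the protocol does not state the amount), at most 70 more softgels per man. The statistical price is a slightly wider exposure window for evaluable men, 90 to 104 days instead of 90 to 98. Aligning both limits at 98 days would also be consistent, but it would keep excluding men for delays that the protocol regards as normal, so 104 is the better choice.
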